### Interim analyses {21b}

Not applicable. Interim analyses are not planned within the study protocol, given the relatively short study period, and blinding will be maintained throughout the study. Termination of the study is unlikely, as there are no new interventions involving novel pharmacological substances or treatments. Nevertheless, study termination may be considered if recommended by the ethics board.

### Methods for additional analyses (e.g., subgroup analyses) {20b}

This is not applicable to our study, as no subgroup analyses are planned.

### Methods in analysis to handle protocol non-adherence and any statistical methods to handle missing data {20c}

In the event that patients choose to discharge themselves from the hospital before their scheduled follow-up visit, they will be requested to perform third-party assessments using the MADRS, HDRS-24, DOTES scales, and report their medication/treatment status on the day of discharge. Additionally, they will be queried about the feasibility of conducting a follow-up over the phone using the same set of questionnaires. However, if missing values occur in one of the two co-primary endpoints, they are addressed in the following way: Missing values in the 1st primary endpoint “Remission Rate” are defined as “Treatment Failures” and missing values for the endpoint “AE rate” are defined as having “Had at least one adverse event.”

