### Outcomes {12}

#### Primary outcome

Two co-primary endpoints are used for evaluating the predictive value of BDNF -87 methylation. The 1st co-primary endpoint is the rate of patients achieving remission during therapy, defined as a score of ≤ 10 on the Hamilton Depression Rating Scale (HDRS-24) on day 49 (± 3). The HDRS-24 is commonly used in clinical trials for depression and remission is considered the most relevant outcome for patients. Achieving remission indicates a higher likelihood of full recovery, improved quality of life, and reduced risk of experiencing a chronic-recurrent form of depression. This endpoint focuses on the absence of residual symptoms rather than just a partial response.

The 2nd co-primary endpoint is the rate of AEs. For evaluating AEs an extended version of the DOTES is used on a weekly basis. If a patient has at least one AE with an intensity of three within the time interval of 49 (± 3) days, it is counted for the co-primary endpoint.

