#### 2nd co-primary endpoint (AE rate)

In a meta-analysis conducted by [21], which examined the efficacy of SSRIs and the incidence of AEs based on placebo-controlled studies, the median AE rate was 0.8 in the treatment group. In this trial, it is assumed that knowing the marker status will result in a reduced use of antidepressants, leading to fewer AEs during pharmacotherapy. Conservatively, it is assumed that the AE rate will be half in the biomarker-negative group compared to the rate in patients treated with antidepressants (AE rate in antidepressant-treated patients: 0.8, AE rate in patients not treated with antidepressants: 0.4). Therefore, it is assumed that the AE rate in the marker group is 0.6, calculated as the mean of the expected AE rates stated. Since all MDD patients in the TAU group receive antidepressant treatment, an AE rate of 0.8 is assumed. A sample size of 218 achieves 90% power to detect a rate difference of − 0.20 (marker − TAU group) for the assumed AE rates, with a one-sided type I error of 2.5%.

To demonstrate the value of knowing the marker status for both co-primary endpoints with sufficient robustness, the final sample size was determined based on the 1st primary endpoint, which requires a larger sample size (*n* = 222 vs. *n* = 218). To compensate for potential treatment effect reduction due to study dropouts, the sample size is increased by 15% to ensure a conservative sample determination (*n* = 256). Sample size calculation was performed with nQuery 9.3.

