### Implementation {16c}

The study physician at each site will receive notification once the randomization for a patient is finalized. The allocation will be disclosed to the patient and the treating physician, but it will remain concealed from the rater who is blinded to the study group.

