### Plans to promote participant retention and complete follow-up {18b}

Patients will be in the psychiatric ward for a minimum of 49 days. Participation in this diagnostic trial will only impact treatment if the marker status is known. However, the decision on the chosen treatment strategy will ultimately rest with the treating physician and the patient. The study protocol does not provide guidance on the treatment.

In the event of withdrawal from the study, a brief retention follow-up, including MADRS, HDRS-24, DOTES, and current treatment modalities, will be conducted. To ensure data quality for the co-primary endpoints, a phone follow-up will occur on day 49 ± 3, collecting MADRS, HDRS-24, DOTES, and information on current treatment modalities.

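### Scoring every missing AE endpoint as an AE is neutral only if missingness is equal between arms; higher missingness in TAU would inflate the chance of a false AE superiority claim

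*Protocol article*

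**What the plan says.** The 2nd co-primary endpoint (Outcomes {12}) is binary: a patient counts if weekly DOTES shows "at least one AE with an intensity of three" within 49 (± 3) days. The aim is superiority, met when the upper 95% confidence limit for marker minus TAU is below 0 (Statistical methods {20a}).

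Sections {20a} and {20c} both fix the missing-data rule for the primary ITT analysis. For the AE endpoint, "missing values for the endpoint “AE rate” are defined as having “Had at least one adverse event". For remission, "Missing values in the 1st primary endpoint “Remission Rate” are defined as “Treatment Failures". The same rule applies in both arms. Neither section says when a partly observed DOTES series counts as missing.

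On blinding, {16c} states: "The allocation will be disclosed to the patient and the treating physician". Only the raters are blinded.

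On retention, {18b} states: "In the event of withdrawal from the study, a brief retention follow-up, including MADRS, HDRS-24, DOTES, and current treatment modalities, will be conducted". It adds a phone follow-up at day 49 that includes DOTES. Under {20c}, patients who discharge themselves are asked for a DOTES on that day and whether a phone follow-up is feasible.

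**The concern.** Counting a missing outcome as the bad outcome is often taken to be conservative. For a between-arm superiority claim it is conservative only in the arm that is meant to win. Here each patient with a missing endpoint becomes an AE event in his or her own arm, so whichever arm has more missing endpoints gains more events. If that arm is TAU, the gap itself counts as evidence that the marker reduces AEs.

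Open allocation makes a gap possible. TAU patients give the sample but are not told the result; marker patients learn theirs and may react to it. The protocol gives no withdrawal rate by arm.

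The rule may also set aside collected data. A leaver with several weekly DOTES and a withdrawal DOTES, none showing an intensity-three AE, would be scored as an event if the series is classed as missing. At stake is false success on the endpoint that carries the trial's benefit claim, in addition to some loss of power.

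**Working it through.** **Inputs from the protocol.** TAU: "an AE rate of 0.8 is assumed". Marker: "it is assumed that the AE rate in the marker group is 0.6". One-sided 2.5% level, 90% power, N = 218 for AEs, N = 222 for remission, 15% increase to N = 256, 1:1 allocation (Sample size {14}).

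**Assumptions, not in the protocol.** Missing shares by arm, d_M and d_T, chosen to average the planned 15%; the same AE rate p in leavers and completers; AE rates below 0.6.

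**The plan's own figures.** Pooled two-proportion formula, mean rate 0.7:

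n = [1.960 × √(2 × 0.7 × 0.3) + 1.282 × √(0.6 × 0.4 + 0.8 × 0.2)]² / 0.2² ≈ 108.2, so 109 per arm and 218 in total, as stated. 222 × 1.15 = 255.3, so 256, or 128 per arm.

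**Effect of the rule.** The analysed AE rate in an arm is p + d(1 − p). With the same true p in both arms, the expected difference (marker − TAU) is

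−(1 − p)(d_T − d_M).

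It is zero only if d_T = d_M.

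**False superiority.** Unstratified z-test, n = 128 per arm: probability = Φ(−1.96 + |difference| / SE), where SE² = [r_M(1 − r_M) + r_T(1 − r_T)]/128 and r is the analysed rate.

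Example, p = 0.8, 10% v 20% missing: r_M = 0.82, r_T = 0.84, difference −0.02, SE = √[(0.1476 + 0.1344)/128] = 0.0469, so Φ(−1.96 + 0.426) = 6.2%.

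| True AE rate, both arms | 10% v 20% missing: difference | False superiority | 12.5% v 17.5% missing: difference | False superiority |
|---|---|---|---|---|
| 0.8 (protocol, TAU) | −0.02 | 6% | −0.01 | 4% |
| 0.6 (protocol, marker) | −0.04 | 10% | −0.02 | 5% |
| 0.3 (assumed) | −0.07 | 21% | −0.035 | 8% |

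Exact binomial enumeration for the 10-point gap gives 6.1%, 10.0% and 20.4%.

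**Checks in the other direction.**
- Equal missingness of 15% in both arms: false superiority stays at 2.5%. Under the planned alternative the rates become 0.66 v 0.83, a difference of −0.17, with power about 88%.
- More missing in the marker arm (20% v 10%): false superiority falls to 0.9% at p = 0.8 and 0.4% at p = 0.6.

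**Size of gap needed.** For the expected difference to be significant by itself, TAU missingness must exceed marker missingness by about 42 to 45 points at p = 0.8, or 28 to 29 points at p = 0.6.

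**Leavers unlike completers.** If leavers have a true AE rate q, the rule shifts the difference by −(1 − q)(d_T − d_M). With q = 0.9 and a 10-point gap, that is only −0.01.

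**The case against.** There is a good deal to say for the plan.

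- *The rule is symmetric.* Correct. A reader might infer that it favours the marker arm by construction. It does not: wording and effect are the same in both arms, and equal missingness preserves the 2.5% level. Any bias comes from a gap in missingness.
- *No gap is documented.* Also correct. Nothing shows that TAU patients will leave more often. Listing early leaving as a secondary endpoint is not evidence of a difference. The Discussion foresees confusion among patients who know their marker result, which could point the other way. Its statement that adherence should not differ is about adherence and does not settle withdrawal.
- *Leaving is not the same as a missing endpoint.* The 15% is a dropout allowance. The inpatient stay of at least 49 days, weekly DOTES, the withdrawal DOTES and the day-49 phone DOTES should bring endpoint missingness below the dropout rate. They depend on the leaver's cooperation, so they reduce it without removing it.
- *The clean-DOTES case is an inference.* It follows if a partly observed series counts as missing, but the protocol does not say so.
- *An SAP may exist.* One might infer that no alternative handling is planned. That cannot be concluded, since sensitivity analyses are commonly left to the SAP.

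What remains is that the primary rule, which decides success, is already fixed, and its validity depends on equal missingness in a trial with open allocation.

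**Conclusion.** The point holds in a limited form. The fixed primary rule is not conservative for the AE superiority claim if TAU has more missing endpoints than the marker arm. At the protocol's own AE rates the inflation is modest: about 6% (rate 0.8) to 10% (rate 0.6) for a 10-point gap, and 4% to 5% for a 5-point gap, against 2.5%. It would be larger if intensity-three AEs are less common than assumed. That is plausible, because the 0.8 is a median AE rate from a meta-analysis of SSRI trials while the endpoint counts only intensity three, but the 21% at 0.3 rests on an assumed rate.

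A reader might go further and infer that TAU withdrawals alone would be expected to produce AE superiority. The figures do not support that at the planned rates, where gaps of roughly 28 to 45 points would be needed.

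The results assume 128 per arm, an unstratified test in place of the planned stratified Mantel–Haenszel analysis, leavers with the same AE rate as completers, and missing shares by arm that the protocol does not give.

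**What to change.** 1. Derive the AE endpoint from all recorded DOTES, including the withdrawal and phone DOTES, and count any observed intensity-three AE as an event.
2. State when a partly observed DOTES series counts as missing, including whether a day-49 phone DOTES completes it.
3. For leavers without an observed event, impute only the unobserved weeks, for example by multiple imputation using arm, the stratification factors and the weekly scores already recorded. Other principled methods would also be defensible.
4. Keep missing = AE as a sensitivity analysis.
5. Add a tipping-point analysis, or one set against the hypothesis (missing = AE in the marker arm, no AE in TAU), and interpret the AE superiority claim in its light.

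Cost: protocol or SAP wording and a little more analysis, with no new data. The protocol reports that recruitment has not started, so the change can be made before any outcome is seen. The downside is a model-based primary handling in place of a simple fill-in. If an SAP already contains items 4 and 5, only items 1 to 3 remain.

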### Plans to give access to the full protocol, participant-level data and statistical code {31c}

The study plan is accessible to the public through the German Clinical Trials Register (DRKS-ID: DRKS00032503). For the dataset and statistical code, interested parties may request access from the corresponding author after consultation with the steering committee.

## Oversight and monitoring

### Composition of the coordinating center and trial steering committee {5d}

The trial steering committee are the same as in P4D (NCT06027177; DRKS00032215):

Located at Hannover Medical School (MHH) in Germany, the coordinating center is part of the Department of Psychiatry, Social Psychiatry, and Psychotherapy. Recruiting university hospitals provide a pool of principle investigators and co-principal investigators that make up the trial steering committee. They will provide suggestions for the early termination, modification, or continuation of the study as needed. They are responsible for planning, carrying out, and monitoring the research protocol. In addition to overseeing data entry, investigators are in charge of recruiting patients and making sure the study is conducted correctly. The data manager is responsible for maintaining data integrity, guaranteeing data quality, and arranging data acquisition. Within the P4D consortium, meetings are held every 2 weeks.

### Composition of the data monitoring committee, its role and reporting structure {21a}

In this study, there will be no Data Monitoring Committee, as it is not subject to pharmaceutical law regulations.

### Adverse event reporting and harms {22}

AEs in the diagnostic trial are gathered through weekly assessments using an extended version of the DOTES scale. This scale specifically addresses the most common AEs associated with drugs, ECT, repetitive transcranial magnetic stimulation (rTMS), and intranasal esketamine. Investigators also have the option to report any other adverse events through free-text input.

### Frequency and plans for auditing trial conduct {23}

The Center for Clinical Trials will conduct a site visit to each recruiting center once during the recruitment phase. Moreover, members of the coordinating center will visit each recruiting center before enrolling the first patient to ensure harmonization.

### Plans for communicating important protocol amendments to relevant parties (e.g., trial participants, ethical committees) {25}

Any alterations to the research protocol are implemented with the consensus of collaborating stakeholders and require approval through an amendment by the leading ethics committee of MHH, followed by approval from all involved ethics committees. Once approved, these changes will be communicated and documented in the online protocol registrations. All investigators will be promptly notified of the modifications.

### Dissemination plans {31a}

The proposed study protocol and its results will be disseminated through various communication channels (such as information material, press releases/briefings, publications, conferences/symposia, meetings of interest groups, and social media) throughout the entire project duration. A local coordination office will be established to ensure effective coordination among all participating facilities, dissemination of newly acquired knowledge, and the promotion of precision medicine in routine practice using the newly developed assays. This office will be supported by the GDF and the PAB. The collaboration between clinical, biological, and data scientists, along with a company experienced in providing clinical decision tools, and the GDF as the leading particular interest group for MDD patients, creates a strong network for the rapid translation and dissemination of the findings from the BDNF trial.

A dissemination and communication plan will be developed at the outset, outlining the relevant stakeholder groups and their specific needs and strategies to engage with them. Various dissemination tools will be explored to generate awareness and visibility for the project and effectively communicate the project’s outcomes. These activities will involve all project partners and target the scientific community, clinicians, medical practitioners, regulatory bodies, patient groups, and the general public. Each target group will be approached in a tailored manner to meet their specific requirements. The dissemination plan will be a dynamic document that will be continuously monitored and updated to ensure its relevance and effectiveness.

### Ethics approval

The trial will be conducted in accordance with the principles of ICH-GCP (International Council for Harmonisation of Technical Requirements for Pharmaceuticals for Human Use—Good Clinical Practice) and the Declaration of Helsinki. Ethical approval for the study has been obtained from the leading ethics committee responsible for MHH (No. 10843_BO_S_2023). Each participating center will submit an ethics application to its respective ethics committee and will not begin recruiting until receiving a positive vote. Patients participating in the study will be required to provide written consent. They will be fully informed about the study protocol, the study intervention (including detailed information about the medical procedure), and the potential access to their medical records by monitors, auditors, and regulatory authorities. The access to medical records will be done in a manner that respects patient confidentiality and complies with relevant regulations. Patients will have adequate time to ask questions and seek clarification before deciding to participate. They will also receive information and provide consent regarding data protection and data confidentiality. Participants have the right to withdraw their consent at any time without any negative consequences for their treatment. The personal data of all study participants will be handled in compliance with the GDPR of the European Union. Data will be pseudonymized before being entered into a GCP-validated electronic data capture system called MARVIN (provided by XClinical).

## Discussion

This innovative and pragmatic RCT aims to evaluate whether knowledge of the biomarker BDNF exon IV CpG -87 is non-inferior to TAU in terms of achieving remission, while also demonstrating a reduced incidence of AEs in severely depressed patients. Our proposed biomarker has already been independently replicated in a Chinese cohort [20], making this investigation crucial for confirming or refuting its diagnostic value.

In addition to the data gathered in this study, several notable strengths exist. Firstly, our study design closely resembles real-life situations by having minimal exclusion criteria (see Table 1). This means that patients included in the study have MDD and might experience comorbidities [22–24]. This is advantageous since RCTs often have strict inclusion criteria, and take place in highly controlled settings. In our study, the treating physician will decide with the individual patient the patient’s treatment course, mirroring real-world scenarios. Furthermore, we are conducting weekly assessments, allowing us to closely monitor the progression of the disease and the improvement of symptoms. If successful, this biomarker can spare patients from prolonged suffering by avoiding the trial-and-error approach to AD treatment. Secondly, our study incorporates an innovative design whereby patients are randomized only after analyzing their marker status. This approach enhances the precision of the study. Thirdly, since this trial is part of a more extensive cohort study (P4D: DRKS-ID: DRKS00032215), the data collected can be utilized for further characterization and stratification based on the biomarkers and other clinical characteristics and physiological features of depressed patients. This promising approach enables further refinement of patient stratification according to their unique clinical characteristics. Lastly, the study involves industrial partners who will handle the commercialization and distribution of the biomarker if successful, facilitating its translation into clinical practice.

In addition to the strengths mentioned above, this study has some limitations that should be acknowledged. The absence of long-term follow-up beyond day 70 (± 3) by phone prevents us from drawing conclusions regarding the extended progression of the disease and the sustainability of response or remission. However, AD response after 10 weeks is rare. Furthermore, it is essential to recognize that patients with the CpG -87 marker may still exhibit non-response to medication, potentially leading to confusion or misunderstanding, as their expectations for a positive response to pharmacological treatment may not align with the need for alternative interventions such as neurostimulation. The study’s design, which grants treating physicians the autonomy to select treatment courses for each patient, introduces variability in treatment protocols, posing a challenge in attributing outcomes solely to the biomarker. Additionally, the study may not sufficiently address or account for variations in patient treatment adherence or compliance. This could impact treatment outcomes and complicate the biomarker’s predictive value interpretation. On the other hand, there is no reason to believe, that adherence could differ between groups.

## Trial status

Ethics approval No. 10843_BO_S_2023; Protocol Version Number: 2.0. Recruitment has not yet started. Recruitment will be completed after approximately 18 months.

## Data Availability

The data will be pseudonymized. For the dataset and statistical code, interested parties may request access from the corresponding author after consultation with the steering committee.

## Abbreviations

AD: Antidepressant drug
AEs: Adverse events
BDI-II: Beck’s Depression Inventory II
BDNF: Brain-derived neurotrophic factor
BL: Baseline
Ca: Calcium
Cl: Chloride
CK: Creatine kinase
CpG: 5′—C—phosphate—G—3′
CRP: C-reactive protein
DIPS: Diagnostic Interview for Mental Disorders
DNA: Deoxyribonucleic acid
DOTES: Dosage Record, and Treatment Emergent Side Effects scale
DRKS: German Clinical Trial Register
DTD: Difficult-to-treat depression
eCRF: Electronic case report form
EDTA: Ethylenediaminetetraacetic acid
eGFR: Estimated glomerular filtration rate
gammaGT: Gamma-glutamyl transferase
GDPR: General Data Protection Regulation
GOT: Glutamate oxaloacetate transaminase
GPT: Glutamate pyruvate transaminase
EMC: Early Medication Change study
FU: Follow-up assessment
GDF: German Depression Foundation
HbA1c: Hemoglobin A1c
HDL: High-density lipoprotein
HDRS-24: Hamilton Depression Rating Scale
ICD-10: 10Th revision of the International Statistical Classification of Diseases and Related Health Problems
ICH-GCP: International Council for Harmonisation of Technical Requirements for Pharmaceuticals for Human Use—Good Clinical Practice
ITT: Intention-to-treat
K: Potassium
LDL: Low-density lipoprotein
LUH: Leibniz Universität Hannover
MADRS: Montgomery–Åsberg Depression Rating Scale
MDD: Major depressive disorder
MHH: Hannover Medical School
MINI-DIPS: Mini Diagnostic Interview for Mental Disorders
Na: Sodium
Nds. PsychKG: Lower Saxony Law on Assistance and Protective Measures for the Mentally Ill
PAB: Patient Advisory Board
P4D: Personalized, Predictive, Precise & Preventive Medicine for Major Depression
rTMS: Repetitive transcranial magnetic stimulation
SNRIs: Serotonin-norepinephrine reuptake inhibitors
SSRIs: Selective serotonin reuptake inhibitors
TAU: Treatment-as-usual
TRD: (Pharmaco)treatment-resistant depression
